### Interventions

The intervention in this study is designed to manage and mitigate modifiable risk factors associated with spontaneous PTB among pregnant women. It is implemented as a bundle of low-cost measures across different stages of pregnancy, with a focus on three key areas: smoking cessation, maintenance of healthy vaginal microbiota, and management of cervical shortening.

Below is a detailed description of each component of the intervention:(1) First Trimester (11 to 13 weeks and 6 days): Assessment and Smoking Intervention.**Sociodemographic and Clinical Assessment**: During the first trimester, participants undergo an initial interview to collect personal, social, and clinical information. This includes family and obstetric history, as well as smoking status.**Smoking Cessation Support**: Pregnant women identified as smokers who are willing to quit are provided with a comprehensive smoking cessation program. This includes referral to the city’s smoking prevention program, which is conducted at the Alcohol and Drug Psychosocial Care Center (CAPS-AD).The smoking intervention involves an initial interview and adjuvant treatment with auricular acupuncture. This technique uses pressure points in the ear to help reduce anxiety and withdrawal symptoms associated with smoking cessation.Acupuncture sessions are conducted every 15 days, where seeds are placed on specific points in the ear to stimulate them. Cotton and 70% alcohol are used to clean the ear, an auricular pressure gauge is used to locate the points, and mustard seeds with micropore are placed for acupressure of the selected points. The patients are instructed to stimulate these points themselves three times daily. Auriculotherapy is delivered by a trained and certified professional. Patient engagement is monitored by tracking attendance, with the number of appointments systematically recorded in the medical records.If necessary, group sessions with psychological support are provided at CAPS-AD, and pharmacological treatment, such as nicotine patches, may be used for gradual dose reduction to alleviate withdrawal symptoms.2. **Second Trimester (20 to 23 weeks and 6 days): Cervical Length Monitoring and Infection Treatment**.**Cervical Length Screening**: Between 20 and 24 weeks of gestation, all participating women undergo a transvaginal ultrasound to measure cervical length, a critical indicator of the risk for PTB.The measurement is taken with the patient in the lithotomy position, using a transvaginal probe to assess the distance between the internal and external orifices of the cervical canal. Women are instructed to empty their bladder before the ultrasound evaluation.Three consecutive measures are taken and the smallest value is considered. If a cervical length of less than 25 mm is detected, the woman is diagnosed with cervical shortening.Women diagnosed with cervical shortening are prescribed 200 mg of vaginal progesterone daily until 36 weeks of gestation, aiming to reduce the risk of PTB. For these women, the measurement is repeated biweekly for follow-up and monitoring treatment adherence.For cases of severe cervical shortening, such as lengths below 15 mm, cerclage – a surgical procedure to reinforce the cervix – is considered, depending on the patient’s clinical history and ongoing evaluations.**Investigation and Treatment of Infections**: During the same trimester, women are also screened for lower genital tract infections using molecular tests for *Chlamydia trachomatis* and *Neisseria gonorrhoeae*. These investigations are performed at this time due to the less friable nature of mid-trimester cervices in comparison to the first trimester of pregnancy.The assessment includes a complete gynecological examination with swabs for Gram staining, vaginal pH measurement, and cytobrush sampling collection for PCR analysis of cervical infection using the automated Cobas® 4800 CT/NG v2.0.Identified infections are treated according to the local clinical protocols to ensure the health of both the mother and the fetus.

**3. Throughout All Trimesters (11 weeks to Term): Vaginal Microbiota Monitoring and Dysbiosis Management.**

**Quarterly Assessment of Vaginal Microbiota**: During each trimester, vaginal samples are collected from the vaginal wall using sterile swabs to assess eubiosis (the balance of the vaginal microbiota) by bacterioscopy using the Gram staining method according to the criteria set by Nugent et al. [11].The microscopic evaluation aims to identify dysbiosis, such as bacterial vaginosis, candidiasis, or other alterations in the vaginal microbiota. The trained examiner will be blinded to patients’ clinical symptoms and a quality assessment of the readings will be performed by an independent examiner, following the same criteria.Women diagnosed with dysbiosis receive treatment based on the type of condition identified. For bacterial vaginosis, standard antibiotic metronidazole 500 mg orally 12/12 h for 7 days regimens are administered. Recurrent cases are treated with metronidazole gel 0.75% 5 g intravaginally once a day for 5 days or Clindamycin cream 2% (20 mg/g) 5 g intravaginally at bedtime for 7 days, according to the CDC protocol, and the partner is treated with secnidazole orally 1000 mg, single dose.Standard antifungal treatment provided for candidiasis is topic nistatin for seven nights. Recurrent cases are treated with miconazole 2% cream 5 g intravaginally daily for 14 days.Additionally, all participants are educated on proper intimate hygiene practices to help maintain a balanced vaginal environment throughout the pregnancy.

This protocol is conducted alongside standard prenatal care and patients are periodically reminded of their appointments. The study protocol is original and was registered in the Brazilian Clinical Trial Registry (ReBec) on 29 October 2024 (approval pending).

Data regarding the appointments, patients’ compliance with the protocol, and pregnancy outcome will be collected through interviews and medical records by the researchers for subsequent analysis. Data entry will be double checked, periodically updated and securely stored in the institutional repository. Only the researchers will have access to individual-level data, while metadata will be made openly available after publication of the study results.

### Analysis plan

The main outcome of interest is gestational age at birth, based on first-trimester ultrasound, to be compared between the participants of the study and the general population. For the analysis, gestational age will be treated as categorical data (preterm birth vs. term birth). The primary analysis will follow the intention-to-treat principle: participants will be analyzed according to the assignment of their cluster at the time of inclusion. Secondary analyses will consider gestational age at delivery (continuous, in days) and other perinatal outcomes.

Secondary outcomes include the percentage of pregnant women included, the percentage of complete follow-up, percentage of adherence to prescribed treatments, and neonatal outcome (Apgar score, birth weight, and length of stay in the Intensive Care Unit). Descriptive statistics will be performed to analyze clinical, biological, and sociodemographic data of the studied population. Vaginal microbiota status across the trimesters will be compared using the Chi-square test.

Logistic regression will be performed to evaluate the role of the protocol in reducing PTB. To minimize multiplicity in the analysis and interpretation, covariates for adjustment such as parity, maternal age, and socioeconomic status will be included. The primary effect estimate will be obtained from mixed-effects logistic regression models including a random intercept for cluster and fixed effects for period and pre-specified baseline covariates (maternal age, parity, socioeconomic status). Additional per-protocol analyses will be performed as sensitivity analyses and will include participants who received the defined intervention components. Missing data in covariates will be handled using multiple imputations (MICE) under a missing-at-random assumption. The level of significance adopted for the tests used will be 5%, using *Prism* 5.0 (GraphPad Software).

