## Background

Preterm birth (PTB), defined as birth before 37 weeks of gestation, is associated with perinatal morbidity and mortality worldwide. Preterm newborns are more likely to have short- and long-term complications, such as neurological impairment and increased susceptibility to infections, which can lead to irreversible sequelae and reduced quality of life [1].

Worldwide, the prevalence of PTB is approximately 11% [1], and Brazil is one of the most affected countries, with over 308,700 children born preterm every year, accounting for a preterm birth rate of 11.5%. In São Paulo state, 12% of births in 2023 were preterm, and a higher percentage was reported in the municipality of Jaú, where this adverse outcome affected 13.5% of all pregnancies [2].

PTB is a syndrome of multifactorial etiology with significant activation of inflammatory, oxidative stress, and senescence pathways [3]. PTB prevention should be a priority in public health policies; however, despite all the scientific and clinical efforts to fully elucidate and prevent PTB, protocols for early identification and effective management of women at risk have not yet been well-defined or effectively implemented, especially in Brazil. The main barrier to the implementation of such strategies is the gap in knowledge and communication between researchers, health professionals, and policymakers. In this context, three modifiable risk factors stand out for their well-established association with PTB: smoking habit, vaginal dysbiosis, and cervical shortening [4–9].

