## Methods

### Study design

This is the protocol of an ongoing implementation study with a quasi-experimental controlled trial design conducted with pregnant women from primary health care units in the municipality of Jaú. The city of Jaú, located in the central region of the state of São Paulo, has a population of 151,881 inhabitants and 16 Basic Health Units (UBS) and Family Health Units (USF), in addition to a high-risk pregnancy clinic, Gestar, where this project is implemented.

The 16 UBS/USF were considered clusters and will be included in the study at different stages, according to the stepped wedge model, in which the clusters are gradually transferred to the intervention group at regular intervals until all have been transferred. This design is particularly useful in situations where the intervention cannot be implemented simultaneously for all units due to time, logistics, or ethical constraints [10]. In the first phase, eight of these clusters were randomly selected using a simple randomization process to receive the intervention, focusing on pregnant women during their first trimester. Over time, the remaining clusters will be randomly assigned to transition into the intervention group at regular intervals, using the same simple randomization method, ensuring that by the end of the study, all clusters will have received the intervention (Figure 1). This approach allows for a structured, phased implementation of the intervention, accommodating logistical and ethical constraints, and enables the comparison between clusters that have and have not yet received the intervention during the initial stages of the study.

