**Figure 1. f0001:**
[figure not shown]
Temporal flowchart of cluster inclusion (health units) in the quasi-experimental design study.

During the first 18 months, all first-trimester pregnant women from eight randomized UBS/USF (clusters) are being included. In the next step of the study, 2 UBS/USF per month will be included until all primary care units (clusters) in the municipality are included, as demonstrated in Figure 1.

All pregnant women of eligible gestational age from the eight initially randomized health units were systematically invited to participate in the study and referred to Gestar. Cluster randomization was performed using a randomization tool (https://www.random.org/). Allocation was concealed and known exclusively by the coordinating researcher until implementation, minimizing the risk of selection bias. All participants included in the study will be monitored until the gestational outcome through three appointments, one in each gestational trimester. The inclusion criteria for the study are singleton pregnancy and gestational age between 11 weeks and 13 weeks and 6 days at the first appointment, defined by ultrasound. Pregnancies with fetal death and those attending fewer than two study appointments (first and second trimester) will be excluded from the study.

Considering the intervention aims to reduce the preterm birth rate from 18% (baseline rate, DataSUS) to 11.5% (São Paulo state rate = target rate), with 95% confidence, 5% margin of error, and 80% statistical power, the minimum sample size calculated is 201 patients (SAS 3.0 software). Adjusting the sample size to account for cluster effects (DE = 1+(m − 1)×ICC, where DE: design effect; mean cluster size: *m* = 20; intra-cluster correlation coefficient: ICC = 0.01), the conventional individual-based sample of 201 increased to 240. Considering a 20% loss to follow-up, the final sample size will be 300 participants.

To reduce cross-contamination, clinical procedures are centralized at a reference site (Gestar), and the distribution of printed and digital protocols to the Health Units are restricted until activation. A 2-week operational wash-in with adherence monitoring was implemented.

This project was approved by the Research Ethics Committee of Unoeste – Universidade do Oeste Paulista (CAAE 63,623,922.70000.5515). All patients involved will be informed about the research and sign the informed consent form.

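### The analysis plan names the general population as comparator for the main outcome, which conflicts with the stepped-wedge contrast and with the plan's own primary mixed model

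*Protocol article*

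**What the plan says.** The article describes the main comparison in more than one way.

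- **Analysis plan, opening sentence.** Gestational age at birth, analysed as preterm versus term, is "to be compared between the participants of the study and the general population". That population is not defined further.
- **Study design.** The phased roll-out over 16 units is justified because it "enables the comparison between clusters that have and have not yet received the intervention during the initial stages of the study".
- **Analysis plan, later sentences.** Under intention to treat, "participants will be analyzed according to the assignment of their cluster at the time of inclusion". The primary effect estimate comes from "mixed-effects logistic regression models including a random intercept for cluster and fixed effects for period", plus baseline covariates. No intervention term is named.

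On who supplies data, the text after Figure 1 says: "All pregnant women of eligible gestational age from the eight initially randomized health units were systematically invited to participate in the study". Two further units per month join after 18 months. The Interventions section has all participating women undergo the bundle's cervical screening. No source of data on women in waiting units is described.

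The sample size paragraph sets the aim as a fall in the preterm birth rate: "reduce the preterm birth rate from 18% (baseline rate, DataSUS) to 11.5% (São Paulo state rate = target rate").

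**The concern.** A comparison of participants with the general population and a comparison of active with waiting clusters are different estimands with different data sources. Nothing says which one takes precedence. The mixed model cannot reconcile them, because a published population rate has no cluster, period or individual covariate values.

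If the general-population sentence governs, the comparison is not randomized, and the two sides differ in several ways besides the bundle:

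- Participants are consenting women with singleton pregnancies, seen between 11w0d and 13w6d and dated by ultrasound.
- Fetal deaths and women with fewer than two study appointments are removed after entry.
- The population rate is not said to carry any of these restrictions, nor to cover the same calendar months.

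A lower preterm rate among participants could then arise without any effect of the bundle. What is at stake is whether the primary result can be attributed to the intervention at all.

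**Working it through.** **1. The stated sample size, and which contrast it fits.** Inputs from the sample size paragraph: 18% versus 11.5%, 80% power, 95% confidence (sidedness not stated), m = 20, ICC = 0.01, 20% loss.

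- The later steps reproduce. Design effect = 1 + 19 × 0.01 = 1.19; 201 × 1.19 = 239.2, stated as 240; 240 / 0.8 = 300.
- Two groups, two-sided 5%: n per arm = [1.96√(2 × 0.1475 × 0.8525) + 0.842√(0.18 × 0.82 + 0.115 × 0.885)]² / 0.065² = 467 after rounding up (497 with continuity correction). One-sided: 367 (398 corrected).
- One sample against a fixed 18%: n = [z√(0.18 × 0.82) + 0.842√(0.115 × 0.885)]² / 0.065² = 247 two-sided and 192 one-sided (207 with continuity correction).
- The paragraph also mentions a margin of error ("with 95% confidence, 5% margin of error, and 80% statistical power"). A single-proportion precision formula, 1.96² p(1 − p) / 0.05², gives 227 at 18% and 156 at 11.5%; it yields 201 only near p = 0.155, a rate the article does not state.

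So 201 is not reproduced exactly from the stated inputs. The nearest matches are single-sample calculations, and no two-group version comes close.

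**2. What a fixed external comparator could do (illustration).** Assume that the comparator is a fixed 18%, the bundle has no effect, 201 is the effective number of women, and the test is two-sided at 5%. A reduction is declared when the observed rate is below 0.18 − 1.96√(0.18 × 0.82 / 201) = 0.1269.

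The Background gives a lower figure for Jaú: "in the municipality of Jaú, where this adverse outcome affected 13.5% of all pregnancies". If participants' untreated rate is 13.5%, then z = (0.1269 − 0.135) / √(0.135 × 0.865 / 201) = −0.34, and the probability is 0.37. The gap of 18 − 13.5 = 4.5 points is 69% of the 6.5-point target.

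| Untreated rate in participants | Comparator | Chance of a declared reduction, n = 201 |
|---|---|---|
| 12% | 18% | 62% |
| 13.5% | 18% | 37% (44% at n = 240) |
| 15% | 18% | 18% |
| 16.7% to 17.3% | 18% | about 6% to 4% |
| 18% | 18% | 2.5% (nominal) |
| 13.5% | 13.5% | 2.5% (nominal) |

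The 16.7% to 17.3% row is the shift from restricting to singletons alone, (0.18 − f × p) / (1 − f). It assumes, from outside the article, that multiples are f = 2% to 3% of births with p = 50% to 60% preterm.

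**3. What the randomized contrast would need.** Treating it as a parallel cluster comparison, which is not a full stepped-wedge calculation: 467 × 1.19 = 556 per arm; 556 / 0.8 = 695 per arm; about 1,390 in total. With 240 evaluable women split 120 and 120, power is about 29% ignoring clustering. With 201 effective women in each group it is about 45%.

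**The case against.** The strongest reply is that the article names a source for the primary effect, and it is not the general population. The mixed model and the analysis by cluster assignment are stepped-wedge elements that agree with the Study design section, while the general-population phrase sits in the sentence introducing the outcome and has no test attached. This stands: the bias is conditional on that sentence governing.

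Three stronger readings are tempting and should be resisted.

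- **Every participant receives the intervention, so the model has no controls.** A reader might infer this from the enrolment text and from the screening of all participating women. It is plausible but not stated. The article is silent on waiting units, outcomes come partly from medical records, Figure 1 is not visible, and a fuller protocol may name a control source.
- **The false-success rate is 37%.** The Analysis plan never says the general population means 18%; that figure is the sizing baseline. The Abstract gives 13.4% to 18% for Jaú. The gap between 18% and 13.5% is largely a question about the baseline, separate from the choice of comparator.
- **The bias must favour the bundle.** That direction is likely but not certain. Participants counted within the population rate would dilute the contrast rather than inflate it.

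The Discussion also concedes selection by voluntary participation and calls the design quasi-experimental. That disclosure does not settle which comparator applies.

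**Conclusion.** The point holds as a contradiction in the current text. One sentence makes the general population the comparator for the main outcome; the Study design section and the rest of the Analysis plan imply active versus not-yet-active clusters. It should be resolved before analysis because it decides what the primary result means.

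The consequence is conditional. If the external comparison governs, the randomization of units is not used and non-bundle differences can be read as benefit. The enrolment text, the absence of a described control source and the sizing against DataSUS make that outcome realistic, but none of them proves it is intended.

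No single size can be put on the bias. It depends on two things the article leaves open: which rate serves as comparator, and what participants' untreated rate would be. Among the scenarios shown, a false declaration of benefit ranges from the nominal 2.5% to 37% at Jaú's 13.5%, and higher if the untreated rate is lower still.

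**What to change.** - Remove the general-population comparison as the main contrast and report DataSUS rates as descriptive context only.
- State that the primary effect is the coefficient of an intervention indicator (cluster active at the woman's inclusion, yes or no) in the mixed logistic model with period effects.
- Name the control data: eligible pregnancies from not-yet-active units, taken from routine records under the same eligibility and dating rules as far as the records allow. Waiting units hold no study appointments, so the text must say how the exclusion for fewer than two appointments is handled to keep the two sides alike.
- Restate the power for this contrast. The stated 80% cannot be carried over, since 201 fits no two-group calculation with the stated rates.

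**Cost.** Changes to protocol and analysis plan wording, abstraction of records in the waiting units, and probably an ethics amendment. Control covariates and ultrasound dating may be less complete than those of participants. The restated power may turn out well below 80% unless enough control and intervention pregnancies can be included, and the team should accept that openly. Waiting-unit data are best secured before those units switch.

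### The analysis plan names the general population as comparator for the main outcome, which conflicts with its own primary mixed model and with the stepped-wedge design

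*Protocol article*

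**What the plan says.** The Analysis plan opens by naming gestational age at birth, dichotomised as preterm or term, as the main outcome, "to be compared between the participants of the study and the general population". It gives no area, calendar period or data source for that population.

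The same section then describes a different comparison. Under intention to treat, "participants will be analyzed according to the assignment of their cluster at the time of inclusion". On estimation: "The primary effect estimate will be obtained from mixed-effects logistic regression models including a random intercept for cluster and fixed effects for period", plus maternal age, parity and socioeconomic status.

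Study design supports the second comparison. It says the phased roll-out "enables the comparison between clusters that have and have not yet received the intervention during the initial stages of the study".

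Two statements after Figure 1 also matter:

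- **Inclusion.** For the first 18 months, "all first-trimester pregnant women from eight randomized UBS/USF (clusters) are being included". Two further units then join each month "until all primary care units (clusters) in the municipality are included". No inclusion of women from units still waiting is described.
- **Sample size.** The aim is to "reduce the preterm birth rate from 18% (baseline rate, DataSUS) to 11.5% (São Paulo state rate = target rate"). Power is set at 80%, the confidence level at 95% and the margin of error at 5%. This gives 201 women, raised to 240 for clustering and to 300 for 20% loss.

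**The concern.** One outcome has been given two comparators that answer different questions. The population comparison treats participants as a single exposed group and sets them against an outside rate. The mixed model needs exposed and unexposed women within the 16 units, each with a cluster, an inclusion period and covariates. Population births have none of these, so the two sentences cannot describe the same analysis.

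Only the within-trial comparison uses the random order in which units receive the bundle. The population comparison is an uncontrolled contrast with a rate that has not been chosen. If it were reported as the test of the main outcome, the apparent effect would depend on which rate was picked, and that choice could be made after the participants' rate was known.

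**Working it through.** **1. The two comparisons side by side**

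| | Population sentence | Primary effect estimate |
|---|---|---|
| Exposed | All participants | Women included in activated units |
| Unexposed | General population, undefined | Women included in units not yet activated |
| Cluster and period terms | Not possible for population births | Required |
| Covariates | Not available | Maternal age, parity, socioeconomic status |
| Uses the randomisation | No | Yes |

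**2. How far the population result depends on the rate chosen**

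Inputs: 18% (baseline in the sample-size paragraph); 13.5% (Jaú, Background); 12% (São Paulo state in 2023, Background); 11.5% (Brazil in Background, but labelled the state rate in the sample-size paragraph). Suppose participants reach the 11.5% target exactly. The difference is 11.5 minus the comparator. The odds ratio is (0.115/0.885) divided by p/(1-p), with 0.115/0.885 = 0.1299.

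| Comparator | Difference (points) | Odds ratio |
|---|---|---|
| 18% | 11.5 - 18 = -6.5 | 0.1299/0.2195 = 0.59 |
| 13.5% | 11.5 - 13.5 = -2.0 | 0.1299/0.1561 = 0.83 |
| 12% | 11.5 - 12 = -0.5 | 0.1299/0.1364 = 0.95 |
| 11.5% | 0 | 1.00 |

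The same trial result therefore runs from the full planned effect to none.

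**3. Which comparison the sample size fits**

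One-sample test against a fixed p0 = 0.18, with p1 = 0.115:

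n = [zα√(p0(1-p0)) + zβ√(p1(1-p1))]² / (p0-p1)²

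- One-sided 5%, 80% power: (1.645 × 0.3842 + 0.8416 × 0.3190)² / 0.065² = 191.9, so 192. With continuity correction, (191.9/4) × [1 + √(1 + 2/(191.9 × 0.065))]² = 207.
- Two-sided 5%: (1.960 × 0.3842 + 0.8416 × 0.3190)² / 0.065² = 247, or 262 with correction.

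Two-group comparison of 18% with 11.5%, pooled variance under the null, 80% power:

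- Two-sided: [1.960 × √(2 × 0.1475 × 0.8525) + 0.8416 × √(0.1476 + 0.1018)]² / 0.065² gives 467 per group, 934 in total.
- One-sided: 367 per group, 734 in total.

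The stated 201 lies between 192 and 207 and is far from the others. The later steps reproduce: 1 + 19 × 0.01 = 1.19; 201 × 1.19 = 239.2, so 240; 240/0.8 = 300.

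Power of the one-sided one-sample test at n = 201 is 81.8% against 18%. Against 13.5% it is 19.1%. A plain two-group comparison with 201 women in total, split equally, has 25% power two-sided and 36% one-sided.

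**4. Possible overlap of participants with the population figure**

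If participants are a share f of the births behind the population rate, the observed contrast is (1-f) times the contrast with non-participants. For 6.5 points:

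- f = 0.05 gives 6.2; f = 0.10 gives 5.9; f = 0.25 gives 4.9.
- **Concurrent Jaú figure.** The article gives no number of births. Assume 10 to 13 births per 1,000 among its 151,881 inhabitants, over 18 to 22 months (18 + 8/2 = 22). Then births number 151.881 × 10 × 18/12 = 2,278 to 151.881 × 13 × 22/12 = 3,620. The share is 300/3,620 = 8% to 300/2,278 = 13%, and 6.5 points becomes 6.0 to 5.6.
- **National figure.** 308,700/0.115 is about 2.68 million births a year, so 300 participants are about 0.01%.
- **Pre-study figure.** f = 0.

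**The case against.** The best defence is that the section does rank its analyses. Intention to treat by cluster assignment is called primary, and so is the estimate from the mixed model. The population sentence only introduces the outcome and carries no test, model or primary label. With Study design alongside, a reader can tell which comparison is meant. This stands: the two are not equally ranked primary analyses, and a reader who inferred that the plan allows either to be the headline would go too far. It does not remove the fault. The section still states a comparator for the main outcome that its own model cannot accommodate, and a fuller plan could not agree with both sentences. Nor is this detail lost in condensing for a journal, since the article itself supplies the comparator.

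Two other inferences are tempting and not supported. One is that the population figure contains the participants, so that the treated are compared partly with themselves. The population is undefined, so overlap is only possible: it is zero for a pre-study rate, negligible for the country, and modest for Jaú under the assumed birth rates. The other is to set waiting units at 18% beside a city rate of 13.5% and read the gap as the disagreement between the two comparisons. The Abstract gives a range of 13.4% to 18% for the setting, but nothing says that the ends apply to the same period. Such a gap would mostly reflect unreconciled baseline rates.

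**Conclusion.** The point holds as an inconsistency that needs correcting. The comparator stated for the main outcome is wrong for the trial's own design and primary model. Against an undefined population, participants at 11.5% could be reported as anywhere from 6.5 points better to no different, using only rates printed in the article.

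The sample size makes a mere slip of wording less likely. The figure of 201 fits, narrowly, only a one-sided test against a fixed 18%, and not a comparison of two groups. The article does not state the formula or the sidedness, so this is the best match among the formulas tried, not proof of what was done.

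The figures of 467 per group and 25% power are for a plain two-group comparison. They show the direction of the problem. A stepped-wedge calculation also depends on the period structure and could give a different number.

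**What to change.** 1. In the Analysis plan, replace the general-population comparator with wording such as: *compared between women included in activated units and women included in units not yet activated, estimated by the mixed-effects logistic model below*. Name this as the only primary contrast.
2. State where outcomes and covariates for women in waiting units come from, including how their gestational age is dated. The article describes inclusion only from units receiving the bundle. If no other women contribute data, every woman is exposed and the model cannot estimate an intervention effect.
3. Keep any population rate as a secondary or descriptive comparison. Fix its area, period and source in advance, and exclude participants' births.
4. Restate the power in Study design for the chosen contrast, with sidedness and period structure. For scale only, the plain two-group figure carried through the article's own steps is 934 × 1.19 = 1,112, then 1,112/0.8 = 1,390, against the planned 300.

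The rewording is cheap. The other costs are real: a data source for waiting units has to be set out, the simple comparison with the city rate is no longer the headline, and the stated power will be less favourable.
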